## Abstract

**Background:**

Obesity is an increasingly prevalent chronic condition that is associated with serious morbidity and mortality. Excess body weight is a risk factor contributing to diseases such as hypertension, heart disease, hypercholesterolaemia, diabetes mellitus, cerebrovascular disease, gall bladder disease, and some types of cancer. Almost all the Western anti-obesity drugs have adverse effects or body weight is regained upon cessation of therapy. Recent studies have found that acupuncture had a similar efficacy as the Western anti-obesity drugs with fewer reported adverse effects. However, these conclusions were limited due to the small sample size and low quality of methodologies of these studies. Therefore, we design this study to explore the effectiveness and safety of acupuncture on weight control.

**Methods/design:**

This is a pilot single-blinded, randomized, sham-controlled trial on acupuncture for body weight control. Seventy-two participants are randomly assigned to the acupuncture group or the control group. Tianshu (ST-25), Daheng (SP-15), Daimai (GB-26), Qihai (CV-6), Zhongwan (CV-12), Zusanli (ST-36), Fenglong (ST-40), and Sanyinjiao (SP-6) are selected as acupuncture points. For the acupuncture group, disposable acupuncture needles will be inserted at a depth of 10–25 mm into the points and electrical stimulation with dense-disperse waves at 50 Hz and 10 V will be applied on the abdominal points. The bodily needles will be retained for 30 minutes. For subjects assigned to the control group, Streitberger’s non-invasive acupuncture needles will be applied to serve as the sham control at the same acupoints with the same stimulation modality, except that the needles are only adhered to the skin instead of inserted. The duration of the treatment is 8 weeks with two sessions per week, and the follow-up period is 8 weeks. The primary outcome is the change in body weight before and after treatment. The secondary outcomes include changes in body mass index, waist circumference, hip circumference, and body fat percentage during the treatment and follow-up period.

**Discussion:**

The study will compare the efficacy and safety of acupuncture with sham acupuncture on weight control, in the hope of obtaining evidence for utilizing acupuncture for body weight control.

**Trial registration:**

NCT02516878. Registered on 30 July 2015.

## Background

Obesity is an increasingly prevalent chronic condition that is associated with serious morbidity and mortality [1]. According to the statistical data of the Centre for Health Protection, Hong Kong SAR in 2013, 36.6 % of the population aged 18–64 were classified as overweight or obese (body mass index, BMI ≥ 23), including 18.8 % as obese (BMI ≥ 25) among all the population. Excess body weight is the sixth most important risk factor contributing to the overall burden of disease worldwide, such as hypertension, heart disease, hypercholesterolaemia, diabetes mellitus, cerebrovascular disease, gall bladder disease, and some types of cancer [2, 3]. Obesity is becoming a global epidemic and common health problem. The weight control treatments commonly used nowadays include behavioural intervention, dietary intervention and physical activity, which require a higher level of self-discipline and take up to 6 months or longer to achieve significant weight change [4]; surgery like the duodenal–jejunal bypass liner, which may cause surgical complications [5]; and anti-obesity medications.

Currently, most of the Western anti-obesity drugs have adverse effects like oily discharge followed by flatus and faecal incontinence for orlistat [6]; headache, nausea and dizziness for lorcaserin [7] or body weight regaining upon cessation of therapy [8]. More people would like to seek help from Chinese herbal medicine (CHM) and/or acupuncture for body weight control, especially from acupuncture because it is safe and does not involve the intake of drugs [9].

Systematic reviews and randomized controlled trials have shown the beneficial effects of acupuncture, including body acupuncture and auricular acupressure [9, 10]. Acupuncture compared with placebo or lifestyle modification had more effectiveness in lowering body weight, BMI and waist circumference and it had a similar efficacy as the Western anti-obesity drugs with fewer reported adverse effects of insomnia, headache or gastrointestinal reactions [10, 11]. Auricular acupressure has been summarized as having the effect of appetite suppression on overweight patients [12], and its efficacy on weight control is higher when combined with body acupuncture [13].

However, these conclusions are limited due to the small sample size and low quality of the methodologies of these studies. Also, there is no restricted research to investigate the combination effects of body acupuncture and auricular acupressure compared to sham acupuncture for body weight control among Hong Kong’s Chinese population. Therefore, we design this single-blinded, randomized controlled clinical trial to explore the effectiveness, efficacy and safety of body acupuncture and auricular acupressure on weight control in Hong Kong.

### Objective

The aim of the study is to assess the efficacy and safety of body acupuncture and auricular acupressure compared to sham acupuncture on body weight control through a pilot randomized controlled study.

## Methods/design

### Study design

This is a pilot single-blinded, randomized, sham-controlled trial on acupuncture for body weight control conducted at Hong Kong Baptist University Chinese Medicine Clinics. Seventy-two participants will be enrolled from the public through advertisements via the university’s website and newspaper. Subjects will be randomly assigned to the acupuncture group or the control group. Treatment will be given with two sessions per week for 8 weeks, and the post-treatment follow-up period will be 8 weeks. The primary outcome is the change in body weight before and after treatment. The total study period will be 16 weeks. The study protocol has been approved by the Hong Kong Baptist University Ethics Committee on the Use of Human Subjects for Teaching and Research (Approval no. HASC/13-14/0266) and registered in ClinicalTrials.gov (NCT02516878). The flow chart of the trial is shown in Fig. 1. The checklist for items in STRICTA 2010 is given in Table 1. Informed consent is obtained from each participant.

**Fig. 1 Fig1:**
[figure not shown]
Participant flow diagram

**Table 1 Tab1:** Checklist for items in STRICTA 2010*

Item	Detail
1. Acupuncture rationale	1a) Style of acupuncture:
	According to systematic reviews and clinical experiences of our principal investigator and co-investigators. Manual and electro-acupuncture based on traditional Chinese medicine theory
	1b) Reasoning for treatment provided, based on historical context, literature sources, and/or consensus methods, with references where appropriate
	1c) Extent to which treatment was varied:
	Standard treatment is used. No variation of treatment among patients
2. Details of needling	2a) Number of needle insertions per subject per session (mean and range where relevant):
	14 needles
	2b) Names (or location if no standard name) of points used (uni/bilateral)
	Bilateral:
	Tianshu (ST-25), Daheng (SP-15), Daimai (GB-26),
	Zusanli (ST-36), Fenglong (ST-40), Sanyinjiao (SP-6)
	Unilateral:
	Qihai (CV-6), Zhongwan (CV-12)
	2c) Depth of insertion, based on a specified unit of measurement or on a particular tissue level:
	10–25 mm
	2d) Response sought (e.g. *de qi* or muscle twitch response):
	De qi
	2e) Needle stimulation (e.g. manual, electrical):
	Manual and electrical — dense-disperse waves at 50 Hz and 10 V
	2f) Needle retention time:
	30 min
	2g) Needle type (diameter, length and manufacturer or material):
	Disposable acupuncture needles (verum acupuncture needles asia-med Special No. 16 with 0.30 × 0.30 mm matching the Streitberger sham needles)
3. Treatment regimen	3a) Number of treatment sessions: 16 sessions
	3b) Frequency and duration of treatment sessions:
	2/week for 8 consecutive weeks
4. Other components of treatment	4a) Details of other interventions administered to the acupuncture group (e.g. moxibustion, cupping, herbs, exercises, lifestyle advice):
	Auricular acupressure with Semen Vaccariae embedded adhesive tape.
	Unilateral auricular points: Hunger, Shen men, Spleen and Stomach
	4b) Setting and context of treatment, including instructions to practitioners, and information and explanations to patients:
	University Clinics
	Participants will be informed about acupuncture treatment in the study as follows: “In this study, acupoints for weight control will be used based on related reports and clinical experience of our investigators.”
5. Practitioner background	5) Description of participating acupuncturists (qualification or professional affiliation, years in acupuncture practice, other relevant experience):
	Hong Kong registered Chinese medicine practitioners having at least 3 years of clinical experience, who have undergone training and are able to provide identical acupuncture treatment in accordance with a predefined protocol
6. Control or comparator interventions	6a) Rationale for the control or comparator in the context of the research question, with sources that justify this choice:
	To assess the efficacy and safety of body acupuncture and auricular acupuncture compared to sham acupuncture
	6b) Precise description of the control or comparator. If sham acupuncture or any other type of acupuncture-like control is used, provide details as for items 1 to 3 above
	- Style of acupuncture:
	Sham acupuncture + Semen Vaccariae embedded tape pressure on non-acupoints at auricular helix
	Table 1 Click here to download Table Table 1.docx
	- Number of needle insertions per subject per session:
	14 sham needles at the same acupoints as the treatment group, and 4 auricular helix points with embedded tape pressure
	- Depth of insertion:
	Needles are only adhered to the skin.
	- Needle retention time:
	30 min
	- Needle type
	Streitberger’s non-invasive acupuncture needles (Gauge 8 × 1.2”/0.30 × 30 mm)
	- Number of treatment sessions:
	16 sessions
	- Frequency and duration of treatment sessions:
	2/week for 8 consecutive weeks

*This checklist, which should be read in conjunction with the explanations of the STRICTA items, is designed to replace CONSORT 2010’s item 5 when reporting an acupuncture trial

### Participants

#### Setting

The study is conducted in the research and clinical centres, School of Chinese Medicine, Hong Kong Baptist University.

#### Inclusion criteria

Patients who meet all of the following criteria will be eligible for the study: men or women aged between 18 and 65 years old; with body mass index (BMI) ≥ 25 kg/m^2^; who have not received any other weight control measures or any medical and/or drug history within the last 3 months.

#### Exclusion criteria

Patients who meet any of the following criteria will be excluded from the study: those with endocrine disease, for example, thyroid disorder, pituitary disorder or sex gland disorder; those with heart disease, for example, arrhythmia, heart failure, myocardial infarction or patients with pacemakers; those with allergy and immunology disease; those having a bleeding tendency; pregnant or lactating women; those having impaired hepatic or renal function; those who have had a stroke or are otherwise unable to exercise.

### Interventions

#### Body acupuncture treatment

Acupuncture intervention will be conducted for two sessions per week over 8 consecutive weeks. According to a systematic review, the highly frequently used acupuncture points in body weight control trials are Zusanli (ST-36), Sanyinjiao (SP-6), Tianshu (ST-25), Fenglong (ST-40), Zhongwan (CV-12) and Qihai (CV-6) [9]. Among them, the traditional effects of the abdominal points are harmonizing gastrointestinal function, regulating Qi circulation and treating localized problems, which would be excessive adipose tissue deposition for the studied subjects. The traditional effects of the points at the lower limbs are stabilizing gastrointestinal function and enhancing fluid drainage. With the clinical experience of our principal investigator and co-investigators, eight body points are chosen: Tianshu (ST-25), Daheng (SP-15), Daimai (GB-26), Qihai (CV-6), Zhongwan (CV-12), Zusanli (ST-36), Fenglong (ST-40) and Sanyinjiao (SP-6). The details of acupoints and their functions are listed in Table 2. The acupuncture treatment will be conducted by a registered Chinese medicine practitioner with more than 6 years of Chinese medicine college education and at least 5 years of clinical experience.

**Table 2 Tab2:** Acupoints of the body and their functions

Acupoint	Classical effects of stimulation
Tianshu (ST-25)	Restoring and harmonizing the flow of energy in the intestines; regulating the Qi; breaking up blocks
Daheng (SP-15)	Expelling cold in digestive system; regulating gastrointestinal functions
Daimai (GB-26)	Directing the Qi down into the lower body; stabilizing and harmonizing the lower tri-energizer (lower Jiao), thus draining dampness
Qihai (CV-6)	Supplementing and regulating Qi and Yang; stabilizing and nourishing the kidneys
Zhongwan (CV-12)	Regulating the stomach meridian, harmonizing stomach Qi; draining fluids
Zusanli (ST-36)	Stabilizing and regulating the stomach meridian, harmonizing Qi and the blood
Fenglong (ST-40)	Transforming body fluids; expelling phlegm
Sanyinjiao (SP-6)	Regulating the spleen, liver and kidney meridian; intensifying and dynamizing fluids circulation

Disposable acupuncture needles (verum acupuncture needles asia-med Special No. 16 0.30 × 30 mm matching the Streitberger sham needles) will be inserted at a depth of 10–25 mm into the points. As electro-acupuncture has been reviewed as having a higher efficiency in weight loss treatment [14], we will deliver electrical stimulation with dense-disperse waves at 50 Hz and 10 V through the electrical acupuncture stimulation instrument (ES-160 6-Channel Programmable Electro-acupuncture) to the abdominal points. The bodily needles will be retained for 30 minutes.

#### Auricular acupressure

Participants of the treatment group will additionally receive unilateral auricular acupressure at four auricular points as Hunger, Shen men, Spleen and Stomach with Semen Vaccariae (Wang Bu Liu Xing) embedded within adhesive tape at each treatment session (Fig. 2). Acupressure will be self-applied by the subjects with repeated pressing of the tape with fingertips for 1 minute per point, thrice per day. The embedded tape will be retained in situ for 24 hours, and then the alternate ear will be treated at the next visit. The four points were most frequently used on overweight treatment as summarized by a systemic review [9]. Clinically, the ear points Spleen and Stomach are used for regulating gastrointestinal function; Shen men, meaning Spirit gate, is used for calming mental conditions; Hunger is used for suppressing the desire to eat and is reported to be particularly effective on weight loss [15].

**Fig. 2 Fig2:**
[figure not shown]
Auricular acupressure points and sham acupressure points

#### Sham acupuncture

For subjects assigned to the control group, Streitberger’s non-invasive acupuncture needles (Gauge 8 × 1.2”/0.30 × 30 mm) will be applied to serve as a sham control at the same acupoints with the same stimulation modality, except that the needles are only adhered to the skin instead of being inserted [16]. The validity and credibility of this system has been well demonstrated [17, 18].

#### Sham auricular acupressure

The Semen Vaccariae embedded tape used in the treatment group will be applied on four non-acupoints at the helix unilaterally and retained for 24 hours, and then the alternate ear will be used at the next visit (Fig. 2). The helix region was suggested to be used as a control in auricular needling and was applied in previous clinical trials [19, 20].

All subjects will be advised to have a regular number of meals daily and not to have any snacks. Meals comprise one bowl of rice (210 g) for subjects > 70 kg and two-thirds of a bowl of rice (140 g) for those < 70 kg, with instructions to eat side dishes balanced with the rice. Also, subjects will be instructed not to perform any exercise other than that required for their daily work.

### Outcome measures

The primary outcome is the change in body weight before and after treatment. The secondary outcomes include changes in BMI, waist circumference, hip circumference and body fat percentage during the treatment and follow-up period. Besides at baseline (0 week), the numbers will be measured every 2 weeks. Both the body weight and body fat percentage will be measured with the Omron Karada Scan HBF-701.

Adverse events will be noted throughout the study, based on participant reports and laboratory tests (whole blood counts, renal and liver functions) if needed. All clinical adverse events will be recorded according to terms of intensity (mild, moderate or severe), duration, outcome and relationship to the study.

### Randomization assignment

Subjects of both groups will be randomly assigned to receive acupuncture (body and auricular acupressure) or control (sham) treatment. For randomization, simple, complete non-sequential random numbers will be generated in advance by a computer program in a block of four, and kept by the principal investigator (PI, [name]). After a patient’s eligibility is confirmed, a randomization number which corresponds to the group allocation will be provided to the acupuncturist by the PI. This arrangement will ensure that the clinical assessor and participants are blinded to the allocation.

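### The randomisation text names two incompatible methods and fixes a single published block of four, with the list held by the PI and allocations given to an unblinded acupuncturist, so upcoming allocations could be foreseen

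*Protocol article*

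**What the plan says.** All of this is in the protocol article. Under Randomization assignment, the sequence is described as follows: "simple, complete non-sequential random numbers will be generated in advance by a computer program in a block of four". The same sentence also names the holder of the list: "random numbers will be generated in advance by a computer program in a block of four, and kept by the principal investigator". Once a patient has been found eligible, "a randomization number which corresponds to the group allocation will be provided to the acupuncturist by the PI". The section concludes: "This arrangement will ensure that the clinical assessor and participants are blinded to the allocation".

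Under Study design there are two arms: "Subjects will be randomly assigned to the acupuncture group or the control group". The allocation ratio is not given. Under Sample size the total is 72. Under Sham acupuncture, the control procedure matches the active one "except that the needles are only adhered to the skin instead of being inserted", so whoever applies the needles knows the arm. Trial status reports that recruitment is under way.

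The number of people delivering treatment is unclear. The section on body acupuncture treatment refers to one practitioner, while item 5 of Table 1 refers to practitioners. Study design and Setting refer to clinics and centres in the plural.

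**The concern.** There are two separate problems.

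First, simple or complete randomisation means that each assignment is independent of those before it. Blocking makes assignments depend on one another so that the arms balance within each block. A sequence cannot be both, and a fuller document elsewhere would not make this sentence correct.

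Second, the stated procedure protects the next allocation poorly. With a small block of known size, anyone who has seen the earlier allocations can sometimes work out the next one. The acupuncturist necessarily learns the arm of each person treated. The PI holds the whole list, and nothing says that the PI stands apart from enrolment. If anyone with this knowledge can influence who is accepted, or when, more motivated volunteers could be steered to one arm. All participants receive meal and exercise instructions, so motivation could plausibly affect weight change, and the effect assumed under Sample size is only 1.56 kg. Motivation is not measured, so the planned ANCOVA with baseline as covariate would not remove that bias.

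**Working it through.** The article gives no predictability figure, so there is none to reproduce. The check enumerates the possible blocks.

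**Inputs from the article:** block size 4; two arms; 72 participants, hence 72 / 4 = 18 blocks.

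**Assumptions not in the article:** 1:1 allocation (two of each arm per block), the same block size throughout, known block starts, and one observer who has seen every earlier allocation.

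**Allocations that are certain.** There are 6 equally likely blocks: AABB, ABAB, ABBA, BBAA, BABA, BAAB.
- Positions 1 and 2 are never certain.
- Position 3 is certain only if the first two are alike: 2 of 6 blocks, probability 1/3.
- Position 4 is always certain.
- Expected number per block: 1/3 + 1 = 4/3. Share: (4/3) / 4 = 1/3.
- Over 18 blocks: 18 × 4/3 = 24 of 72 (33.3%).
- A single block yields 1 certain allocation (probability 2/3) or 2 (probability 1/3). The variance per block is 2/9, so the SD over 18 blocks is √(18 × 2/9) = 2.0.

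**Best guess (always name the arm that is behind; toss a coin when level).**
- Position 1: 1/2. Position 2: 2/3. Position 3: 1/3 × 1 + 2/3 × 1/2 = 2/3. Position 4: 1.
- Sum: 17/6 = 2.833 per block; 18 × 17/6 = 51 of 72 (70.8%).
- With truly simple 1:1 randomisation: none certain, and 36 of 72 (50%) guessed correctly.

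**Sensitivity to the assumptions.**

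| Scheme | Certain in advance | Of 72 | Best guess right |
|---|---|---|---|
| Fixed blocks of 4, 1:1 | 33.3% | 24 | 70.8% |
| Fixed blocks of 6, 1:1 | 25% | 18 | 68.3% |
| Fixed blocks of 8, 1:1 | 20% | 14.4 | 66.6% |
| Blocks of 4, 3:1 | 43.75% | 31.5 | not computed |
| Simple 1:1 | 0% | 0 | 50% |

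If several acupuncturists share one list, each sees only part of the sequence and the share that each can foresee is lower. How much lower depends on how patients are divided, which the article does not say. The holder of the list needs no deduction and can know all 72.

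**The case against.** A reader might infer that a third of allocations are predictable in this trial, full stop. The article does not support that. The figure needs an unstated 1:1 ratio, known block starts and one person who sees every earlier allocation, and Table 1 speaks of more than one practitioner. Nor does the article call the trial single-centre; its wording on clinics and centres is plural. Both points stand, so the one third is a conditional figure.

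A reader might also infer that concealment has failed or that selection bias is present. That goes too far as well. Foreknowledge matters only if its holder influences recruitment, eligibility or timing. Recruitment is by public advertisement, the acupuncturist's stated role is treatment, and several entry criteria are objective, such as age and BMI. Releasing the number only after eligibility is a genuine safeguard. It is partial: it does not stop deduction from earlier allocations, and it does not restrain someone who already holds the list.

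The closing sentence on blinding should not be read as a false claim of concealment. It concerns the assessor and the participants only, and an unblinded needler is consistent with a single-blind design. Likewise, selective entry of heavier volunteers would be partly handled by adjusting for baseline weight; it is unmeasured traits that would escape.

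Finally, a journal article may leave release mechanics, such as envelopes, to the full protocol, so their absence is not held against it. The point rests on what the article states: the method, the block size, the list holder and the recipient of each allocation.

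**Conclusion.** The point holds as a contradiction in wording together with a badly fixed procedure. The contradiction between unrestricted and blocked randomisation is certain and depends on no assumption. The predictability is conditional: on average 24 of 72 allocations certain and 51 of 72 guessed correctly, 15 more than chance (51 − 36), for a single observer of a 1:1 sequence with known block starts. It is lower for each of several acupuncturists and complete for the list holder. Whether this leads to bias depends on who recruits, screens and times entry, which the article neither states nor excludes. The arrangement should be changed, but the text does not show that the allocation has been compromised.

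**What to change.** 1. Describe the method as permuted-block randomisation, state the ratio, and delete the terms for unrestricted randomisation.
2. For participants not yet randomised, generate a new list with randomly varying block sizes (for example 4 and 6) that are not disclosed to those who enrol or treat.
3. Have the list held by existing staff who take no part in eligibility, treatment or assessment, and release each assignment only after consent and baseline weight are recorded.
4. State who recruits and who confirms eligibility.

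The third step matters most. Undisclosed varying sizes take away the certainty, but naming the arm that is behind would still be right between 68.3% (blocks of 6) and 70.8% (blocks of 4) of the time for someone who sees everything. Varying sizes also achieve nothing against a person who holds the list.

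The cost is a new list for the remaining allocations, a change of list holder and a likely protocol amendment. There may also be an imbalance of a few subjects at the end: an unfinished block of 6 can leave the arms at most 3 apart. Sample size, treatment and analysis are unaffected.
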